### Sample size

The sample size was calculated based on the effective rate. An improvement of at least 3 points in the CRS-R was considered an effective treatment. Previous studies found the effective rate of taVNS was 7% (*n* = 14) (7) and of HD-tDCS was 36% (*n* = 11) (21). Assuming the existence of a synergistic effect, the SJS group will have a higher effective rate of 43%, while the sham stimulation group will have no effect. Therefore, the two-sided 2 × 4 chi-square test in PASS (version 15) was used for the sample size calculation of four groups. The test power (1-β) was 80% and the type I error rate (α) was 5%. The calculated effect size W was 0.436, and then a dropout rate of 20% was considered. Finally, a total of 84 patients will eventually be enrolled, and each group will have 21 patients (Figure 2).

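### The printed sample-size inputs do not lead to 84: W = 0.436 needs 58 evaluable patients, which is 73 enrolled (76 in four equal arms), and the stated rates give W = 0.446; the discrepancy is conservative

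*Protocol article*

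**What the plan says.** All the figures stand in the Sample size section of the protocol article. A responder is a patient who gains at least 3 CRS-R points. The inputs are:

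- taVNS: "Previous studies found the effective rate of taVNS was 7" per cent, from a study of 14 patients.
- HD-tDCS: "of HD-tDCS was 36" per cent, from a study of 11 patients.
- Combined stimulation: "the SJS group will have a higher effective rate of 43" per cent.
- Sham: "while the sham stimulation group will have no effect".
- Test: "the two-sided 2 × 4 chi-square test in PASS (version 15) was used for the sample size calculation of four groups".
- Error rates: "The test power (1-β) was 80% and the type I error rate (α) was 5" per cent.
- Effect size and dropout: "The calculated effect size W was 0.436, and then a dropout rate of 20% was considered".

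The result is: "Finally, a total of 84 patients will eventually be enrolled, and each group will have 21 patients". The number of evaluable patients before the dropout allowance is not printed, nor is the formula used for that allowance. The Procedures section builds the randomisation list on 84.

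**The concern.** The section prints everything needed to repeat the calculation: four rates, equal arms, the test, alpha, power, W and the dropout rate. Two links in the chain can therefore be checked: from the rates to W, and from W to 84. Neither closes. This paragraph is the only justification given for the enrolment target. If its figures do not belong together, a reader cannot tell which scenario 84 was sized for, in particular which sham response rate, or what power the trial has for its omnibus comparison.

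**Working it through.** **Inputs.** From the Sample size section: rates 0.07, 0.36, 0.43 and 0 (sham read as 0%); four equal arms; 2 × 4 table, so 3 degrees of freedom; alpha 0.05; power 0.80; dropout 20%.

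**Step 1. W from the stated rates.** With equal arms, W² = mean of (p − p̄)² divided by p̄(1 − p̄).

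- p̄ = (0.07 + 0.36 + 0.43 + 0)/4 = 0.215.
- Squared deviations: 0.021025, 0.021025, 0.046225, 0.046225; mean 0.033625.
- p̄(1 − p̄) = 0.215 × 0.785 = 0.168775.
- W² = 0.033625/0.168775 = 0.1992, so W = 0.446.

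Using the fractions 1/14 and 4/11 in place of the rounded 7% and 36% gives 0.4465, so rounding of the source rates does not explain 0.436.

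**Step 2. Evaluable number.** For a chi-square test with 3 degrees of freedom at alpha 0.05, 80% power requires a noncentrality of 10.903, and N = 10.903/W².

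- Printed W: 10.903/0.436² = 57.4, so 58 (power 80.5%; 57 gives 79.7%).
- W from the stated rates: 10.903/0.1992 = 54.7, so 55.

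The gap in W is thus worth 3 evaluable patients, and the printed W is the more cautious of the two.

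**Step 3. Dropout.**

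| Route | W = 0.436 | W = 0.446 |
|---|---|---|
| Evaluable N | 58 | 55 |
| N/0.8 | 72.5, so 73 | 68.75, so 69 |
| Equal arms, each divided by 0.8 | 15/0.8 = 18.75, so 19 × 4 = 76 | 14/0.8 = 17.5, so 18 × 4 = 72 |
| Multiplying by 1.2 | 58 × 1.2 = 69.6, so 70; 15 × 1.2 = 18, so 72 in equal arms | lower still |

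No route that keeps 3 degrees of freedom, alpha 5% and power 80% exceeds 76. The printed 84 is 84 − 76 = 8 patients (2 per arm, about 11%) above the equal-arm figure and 84 − 73 = 11 above the unrounded one.

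**Step 4. What 84 delivers.** 84 × 0.8 = 67.2, so about 67 evaluable. Omnibus power from the noncentral chi-square distribution:

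- W = 0.436: 86%.
- W = 0.446: 88%.

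**Step 5. Sensitivity to the sham rate.** These sham rates are assumptions, not figures from the article; the other three rates are as stated, with 67 evaluable.

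- Sham 5%: W = 0.404, power about 80%.
- Sham 10%: W = 0.368, power about 72%.

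**The case against.** The strongest reply is that nothing is harmed. The trial enrols more than its stated inputs require, 80% is the power set as the target rather than a claim about what 84 patients achieve, and enrolling above a minimum is not an error. The gap in W is 0.010 and close to immaterial. All of that stands, and it limits the point to one of traceability.

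A second reply is that a journal article condenses, and that an unprinted setting may account for 84. Such settings exist. With W = 0.436, alpha 0.025 gives 68 evaluable, or 17 per arm, and 17 × 1.2 = 20.4 rounds up to 21 per arm. Power of 85% gives 65, again 17 per arm and 21 after the same step. But the article prints alpha 5% and power 80%, and an omnibus chi-square test has no two sides over which to halve alpha. These are possible explanations, each of which would itself need a correction to the text. The evaluable number and the dropout formula could fairly be left to a fuller document; a mismatch among the figures that are printed is not explained by condensation.

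Three stronger readings are tempting and are not supported:

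- A reader might infer that 0.436 came from converting the rates to whole patients out of 21, so that the answer was used as an input. Counts of 2, 8, 9 and 0 out of 21 do give 0.436, but so do 2, 7, 9 and 0 out of 20 (0.4358), and a sham rate of 1% gives 0.437. The source of 0.436 cannot be identified.
- A reader might infer that a 5% sham rate was entered, because it makes 67 evaluable patients give 80% power. Nothing in the article points to this, and it states no effect under sham.
- A reader might infer that the trial misses its 80% power. Under the stated rates the omnibus test exceeds it.

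**Conclusion.** The point holds as a reporting error in the sample-size paragraph. The printed W does not follow from the printed rates (0.446 against 0.436, worth 3 evaluable patients), and the printed total does not follow from the printed W (73, or 76 in equal arms, against 84). The second break is the main one, and it does not depend on the first. The direction is conservative: about 86% to 88% omnibus power with 67 evaluable patients.

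This rests on reading the sham assumption as a 0% responder rate, on equal arms, on the usual noncentral chi-square approximation, and on 20% of the 84 being lost. The power figures concern the four-group omnibus test only and say nothing about comparisons between individual arms. They are also sensitive to the sham rate: the margin is used up at about 5%.

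**What to change.** Keep 84 and rewrite the paragraph so that its figures follow from one another:

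- State the four rates entered in the software, including the sham value, and the W they give: 0.446 if they are the rates now printed.
- State the evaluable number before dropout (55 at W = 0.446, 58 at W = 0.436), the dropout formula and the rounding to equal arms.
- If alpha or power was set to something other than 5% and 80%, say so.
- State the omnibus power that 84 enrolled with about 67 evaluable delivers: about 86% to 88% if sham is 0%. Add a sensitivity line of about 80% if sham is 5% and about 72% if it is 10%, with both sham rates labelled as assumptions.

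The cost is one corrected paragraph. Enrolment, arm sizes, the randomisation list and the planned test do not change.

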### Procedures

The randperm function of MATLAB (Version 2020b, MathWorks Inc., Natick, United States) will be used to generate 84 random integers in random order by the study leader. Each patient will be given a random number in the order of enrollment. The first randomization will divide patients into a combined stimulation group (1–42) and a single stimulation group (43–84) based on a 1:1 ratio. Patients in the combined stimulation group will be further randomized in a 1:1 ratio into the SJS group (1–21) and the sham stimulation group (22–42). Similarly, patients in the single stimulation group will also be randomly assigned in a 1:1 ratio to the taVNS group (43–63) and the HD-t DCS group (64–84).

The study protocol is a double-blind design. Each patient will be exposed to identical-looking simultaneous stimulation. Specifically, the SJS group will receive both positive stimulation of taVNS and HD-tDCS. In contrast, the sham stimulation group will receive sham stimulation of taVNS and HD-tDCS to eliminate potential brain effects caused by the physical compression of the instrument. The patients in the single stimulation group will receive one kind of positive stimulation by taVNS or HD-tDCS. They will also receive sham stimulation of another technique at the same time to blind patients/families and therapists/assessors.

All patients will receive treatment twice a day in the morning and afternoon for 4 weeks. There are 2 days’ rest every 5 days of treatment. Considering the high current intensity of SJS, the single stimulation time of taVNS, commonly for 30 min (24), will be adjusted downward to 20 min to reduce the burden on the patient’s brain.

The Ethics Committee of Beijing Tiantan Hospital will be responsible for independent security monitoring. Adverse events and unintended events will be reported to them when every 10 patients are included. They will further assess the causal relationship between the adverse reaction and treatment. If a serious adverse event is proven to have been caused by the treatment, the trial will be terminated immediately. Appropriate medical emergency and protective measures will be given to patients at the same time.

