**Inclusion**	
	1. Diagnosed with MCS by coma recovery scale-revised;
	2. Age: from 18 to 60 years;
	3. More than 1 month after the initial brain injury;
	4. Consciousness is in a stable phase (no change in the total score of CRS-R) for at least 2 weeks before admission;
	5. No cranial defect or extensive skull repair;
	6. Precuneus and posterior parietal should be intact on at least one side;
	7. Patient-authorized legal representative agreed to the experimental protocol and signed informed consent.

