### Data safety and management

The medical history, demographic data, behavioral data, MRI data, and EEG data of all patients will be stored in the departmental computer database by the study leader. The Ethics Committee of Beijing Tiantan Hospital will regularly check data security.

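### Time since injury and cause, both known at entry, are used in neither the allocation nor the stated comparisons of four arms of 21; this costs precision and interpretability, not validity

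*Protocol article*

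**What the plan says.** **Entry (Table 1).** The time criterion is a floor without a ceiling: "More than 1 month after the initial brain injury". A stability rule goes with it: "Consciousness is in a stable phase (no change in the total score of CRS-R) for at least 2 weeks before admission". Neurodegenerative, operative and malignant causes are excluded; all other causes may enter together.

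**Allocation (Procedures).** The MATLAB permutation function "will be used to generate 84 random integers in random order by the study leader". Numbers 1–21 go to SJS, 22–42 to sham, 43–63 to taVNS and 64–84 to HD-tDCS. The text speaks of a first and a further randomisation, but both are cuts of the same list. No stratification factor, block or minimisation is described.

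**Analysis (Statistical analysis).** Arms are compared by ANOVA or repeated measures ANOVA, by Kruskal-Wallis or Friedman tests, and for counts by chi-square or Fisher tests. No covariate or stratum is named. Baseline CRS-R could enter only as one time point of the repeated measures.

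**Planning (Sample size).** Response is defined thus: "An improvement of at least 3 points in the CRS-R was considered an effective treatment". The planned rates are 7% for taVNS and 36% for HD-tDCS, and "the SJS group will have a higher effective rate of 43%, while the sham stimulation group will have no effect".

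**The concern.** The population may range from patients a few weeks after injury to patients years after it. It is plausible that the chance of a 3-point gain over a 4-week course, treated or not, differs across that range and by cause. The plan itself treats spontaneous change as something to control: it sets the 1-month floor and asks for 2 stable weeks. Those 2 weeks do not cover a 4-week course plus 3 months of follow-up.

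The Discussion expects SJS to show gains by 2 weeks and single stimulation only by 4 weeks. An arm that happened to hold more recently injured patients could imitate or mask that pattern. With 21 patients per arm, such imbalances are not rare, and the stated analysis has no means of accounting for them.

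**Working it through.** **Inputs from the protocol:** 84 patients, four arms of 21; SJS 43%, HD-tDCS 36%, taVNS 7%, sham 0%.

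**Assumptions (the protocol gives no figure):** share of patients early after injury *f* = 30–50%; early-minus-late gap *D* in the probability of a 3-point gain = 10–30 points.

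1. **The plan's benchmark.** 43% − 36% = 7 points, and 0.07 × 21 = 1.5 patients per arm. (The stated total of 84 does not reproduce from W = 0.436: with 3 degrees of freedom and 80% power, 58 are needed, or 73 after dividing by 0.8. That is a separate matter and does not affect this point.)

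2. **Spread of the early share between two given arms.** Sampling without replacement gives SD = √[2*f*(1 − *f*)/21 × 84/83].
   - *f* = 0.5: √(0.0238 × 1.012) = 0.155, about 16 points.
   - *f* = 0.3: √(0.0200 × 1.012) = 0.142, about 14 points.

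3. **Chance of a marked imbalance.** The exact probability that two given arms differ by 5 or more early patients (5/21 = 23.8 points) is 16.7% at *f* = 0.5 and 13.0% at *f* = 0.3, counting both directions.

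4. **Effect on the responder difference.** Shift = (5/21) × *D*, which is 2.4, 4.8 and 7.1 points at *D* = 10, 20 and 30.

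5. **Chance that the expected shift reaches 7 points.** This needs an imbalance of at least 0.07 × 21/*D* patients.

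| *D* | patients needed | *f* = 0.5 | *f* = 0.3 |
|---|---|---|---|
| 10 points | 14.7 | about 0% | about 0% |
| 20 points | 7.4, so 8 | 2.0% | 1.1% |
| 30 points | 4.9, so 5 | 16.7% | 13.0% |

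   Half of each favours SJS: at most about 8% within the assumed range.

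6. **Validity.** With 30,000 re-randomisations under no treatment effect, the unadjusted tests reject in about 4.9% of cases for one pair and 4.8% for four groups.

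7. **Precision to be gained.** With half the patients early and rate *p* = (early + late)/2, the share of outcome variance explained is (*D*²/4)/[*p*(1 − *p*)].
   - Early/late 10%/0%: 0.0025/0.0475 = 5%.
   - 20%/0%: 0.01/0.09 = 11%; the SE of an arm difference falls from 9.3 to 8.7 points.
   - 35%/5%: 0.0225/0.16 = 14%; SE from 12.3 to 11.4.
   - 50%/10% (a 40-point gap, beyond the assumed range): 0.04/0.21 = 19%; SE from 14.1 to 12.7.

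8. **Sampling error for comparison.** For 43% versus 36%, SE = √[(0.43 × 0.57 + 0.36 × 0.64)/21] = 0.150, or 15 points. Power is about 7% at 21 per arm; 80% power would need about 765 per arm.

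**The case against.** The case against has real weight.

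- **No data in the document.** The protocol gives neither the early–late mix nor a recovery rate by time since injury. Taken literally, its sham rate of 0% leaves no spontaneous response to be imbalanced. This stands as a limit on the size of the point. But 0% is a planning assumption, and the plan's own entry rules suggest that its authors did not regard spontaneous change as impossible.
- **Chance imbalance is not bias.** This stands. A reader might infer that the comparison is biased or its tests invalid; step 6 shows otherwise. Randomisation already accounts for such imbalance, and unstratified randomisation is a sound method.
- **Seven points is a weak yardstick.** This also stands. It is 1.5 patients, under half of one SE, and the trial was sized on a four-group test rather than on this pair. A reader might infer that stratifying or adjusting would make SJS versus HD-tDCS readable. It would not.
- **Safeguards exist.** Entry is limited to MCS, ages 18–60 and a preserved target region on at least one side; five assessments before enrolment fix the baseline at the highest score. These narrow the spread, but none uses time since injury beyond the floor, or cause beyond the exclusions.
- **Adjustment may be in an analysis plan that is not shown.** Possible. The unstratified allocation is described in full and is firm. On the analysis, the point concerns the unadjusted tests that the article states.

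A reader might also cite the chance that at least one pair of arms differs by 5 or more early patients, 43–51%. That covers all six pairs and says nothing specific about SJS versus HD-tDCS, for which 13–17% applies.

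**Conclusion.** The point holds as a loss of precision and interpretability. The allocation and the stated tests both ignore two facts known at entry that plausibly bear on the outcome. For a given pair of arms, an imbalance of 5 or more early patients has probability 13–17% if 30–50% of patients are early, and a 5-patient imbalance shifts the expected responder difference by 2.4 to 7.1 points for a gap of 10–30 points.

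The document does not support the stronger reading that imbalance is likely to match the planned SJS advantage. A 7-point shift is practically impossible at a 10-point gap, has a chance of 1–2% at 20 points, and becomes appreciable only near 30 points. Type I error is unaffected. The main obstacle to reading SJS against HD-tDCS is sampling error (SE about 15 points, power about 7%), which this change would reduce only slightly. The change is worth making because it is nearly free.

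**What to change.** **Main change.** Before unblinding, state in Statistical analysis that the arms are compared on CRS-R change and on response with adjustment for baseline CRS-R, log time since injury and cause (traumatic versus non-traumatic). ANCOVA or a mixed model would serve for CRS-R; a stratified or logistic analysis would serve for response. The planned rates imply only about 21 × (0 + 0.07 + 0.36 + 0.43) = 18 responders, with none under sham. An ordinary logistic fit may therefore not converge, and a stratified risk difference or a penalised fit should be named as the method for that case.

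**Cost.** A few degrees of freedom. Time since injury is needed to apply the entry criteria, and medical history is already kept: "The medical history, demographic data, behavioral data, MRI data, and EEG data of all patients will be stored".

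**Only if the list can still be changed.** Enrolment began in April 2023, so this is secondary. Stratify by time since injury, and by cause if feasible, and carry the strata into the analysis. With two time strata and blocks of 4, two arms would differ by about 1 early patient, a shift of about 30/21 = 1.4 points at a 30-point gap. Blocks have a price here. The therapist is told each patient's machine and button number, and each pair of numbers corresponds to one arm, so fixed blocks could make late allocations predictable. Block sizes should therefore vary at random and stay concealed.

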### Stimulations

The stimulation area of the taVNS (SDZ-IIB, Suzhou Medical Supplies Factory) will be bilateral auricles. A pair of clips will be placed on one side of the auricle and another pair of clips will be placed on the opposite side. A clip will have three carbon-impregnated silicone tips. The first tip will serve as the common end of the other two tips to support the posterior surface of the auricle. The second tip will be placed on the lateral scapha. The third tip will be placed on the medial auricular cavity to stimulate targets including cymba conchae and cavum conchae (Figure 1). The stimulator will provide electrical pulses of 1–1.5 mA with an alternate frequency between 4 and 20 Hz and a pulse width of 30 μs. Stimulus intensity will be routinely set at 1.5 mA for each patient. We will turn down the current when the patient’s blood oxygen saturation is below 95%, heart rate increases by more than 20%, or the NCS-R score exceeds 3 points and shows a significant increase during stimulation compared to pre-stimulation. The stimulator will have no ramp-up and ramp-off of current during the stimulation. In addition, two identical-looking instruments will be used. One, called number 1, will be capable of normal stimulation as positive stimulation after the switching on. However, the other one, called number 2, will have no current output as a sham stimulation.

The HD-tDCS (4 × 1-C2, Soterix Medical Inc.) stimulation target will be the precuneus. Pz according to an international standard 10–20 EEG system has been proven as a position overlying the medial parietal cortex and the precuneus (25). Therefore, the central electrode of HD-tDCS is placed at Pz, and the four return electrodes are placed at a distance of approximately 3.5 cm from the central electrode at Cz, P3, P4, and POz (Figure 1). The stimulation current is a constant 2 mA with a ramp-up time of 30 s and a ramp-down time of 30 s. According to simulation modeling from a realistic volumetric approach to simulate transcranial electric stimulation (ROAST) (26), the HD-tDCS montage can effectively activate the PPC and precuneus of patients with DOC (Figure 3A). In terms of sham stimulation of the HD-tDCS, its parameters will be the same as positive stimulation with the difference that the voltage will rise to 2 mA and decrease immediately to 0 mA when the instrument is turned on. The positive and sham stimulation start buttons will be, respectively, covered by two labels called numbers 3 and 4.

### Neuroimaging assessments

T1-weighted brain images will be obtained using a 3.0 T magnetic resonance imaging (MRI) scanner (HD750, GE, United States) to evaluate the resting-state brain structure in each patient before enrollment. Patients with severe damage in the precuneus/PCC will not be included in the study to ensure the effectiveness of HD-tDCS stimulation.

### Behavioral assessments

The CRS-R was first proposed by Giacino et al. (2) to assess the level of consciousness in patients. The scale with a total of 23 points included six subscales of auditory, visual, motor, verbal, communication, and arousal levels (2). In the study, patients will be evaluated independently by two trained clinicians. They will perform five repeated CRS-R assessments at least 2 weeks before enrollment to clarify the patient’s state of consciousness and clinical diagnosis. Finally, the highest CRS-R score will be taken as the pre-treatment (T0) baseline score. Changes in CRS-R will be assessed at three time points during treatment to reflect the effect of treatment: 1 week (T1), 2 weeks (T2), and 4 weeks (T3) (Figure 4).

**Figure 4 fig4:**
[figure not shown]
Treatment and data collection flow diagram. T0: 2 weeks before treatment; T1: 1 week of treatment; T2: 2 weeks of treatment; T3: 4 weeks of treatment; and T4: 3-month follow-up. MRI, magnetic resonance imaging; taVNS, transcutaneous auricular vagus nerve stimulation; HD-tDCS, high-definition transcranial direct current stimulation.

Schnakers et al. (27) developed the nociception coma scale (NCS) to assess the nociception of patients with DOC, which included four subscales of motor response, verbal response, visual response, and facial expression (27). Subsequently, Chatelle et al. (28) excluded the visual subscale to propose a more sensitive new version called NCS-R (ranging from 0 to 9 points) for assessment of nociception compared to the NCS. They found that an NCR-R cut-off value of 4 points could differentiate MCS patients’ behaviors induced by nociceptive stimulation from behaviors induced by non-noxious stimulation (28). The NCS-R will be used before and during stimulation in the study to adjust the current intensity of taVNS.

